### Intervention

#### Drug Characteristics, Distribution, and Storing

A sterile form of racemic ketamine hydrochloride (DIN: 02246795, 02246796) will be dispensed through the Centre for Addiction and Mental Health (CAMH) pharmacy. Ketamine will be administered intravenously over a 40-minute infusion using a Baxter FA-2021-056 pump. The CAMH research pharmacy will order the investigational product from the supplier (Sandoz Canada Inc) on behalf of the research team with the study investigator’s authorization and will be responsible for the receipt and responsible destruction of the investigational product. As per the manufacturer’s recommendation, the investigational product will be stored between 15°C and 30°C, protected from light and heat, and discarded within 28 days of initial use. Only dedicated medical personnel will have access to the investigational product and pick it up from the locked and password-protected storage on the day of the treatment. All treatment sessions will be delivered at CAMH’s Temerty Centre for Therapeutic Brain Intervention, a dedicated clinic providing electroconvulsive therapy to patients and thus equipped with a highly trained medical team.

#### Drug Administration and Scheduling

Ketamine will be administered 2 times per week for 4 weeks (a total of 8 treatment sessions). The dosing schedule will be determined based on the patient’s weight, clinical response, and tolerability (Table 1). The first treatment session dose will be calculated based on 0.5 mg/kg. Doses in this trial will range between 0.5 and 0.8 mg/kg.

**Table 1 table1:** Intervention schedule.

Week	Session, intervention, and dosing
1	Start-up (first) dose to assess tolerability; 0.5 mg/kg intravenous infusion over 40 minutes
	Second infusion session (dose adjustment, if needed, 0.5-0.8 mg/kg)
2	Third infusion session (40 minutes; dose adjustment, if needed, 0.5-0.8 mg/kg)
	Forth infusion session (40 minutes; dose adjustment, if needed, 0.5-0.8 mg/kg)
3	Fifth infusion session (40 minutes; dose adjustment, if needed, 0.5-0.8 mg/kg)
	Sixth infusion session (40 minutes; dose adjustment, if needed, 0.5-0.8 mg/kg)
4	Seventh infusion session (40 minutes; dose adjustment, if needed, 0.5-0.8 mg/kg)
	Eighth infusion session (40 minutes; dose adjustment, if needed, 0.5-0.8 mg/kg)

#### Dose Adjustment

If the first session is tolerated well and the patient has no side effects, the dose can be further increased up to (but not exceeding) 0.8 mg/kg. Participants will have a weekly follow-up with the study’s physician. The study physician will determine the exact doses on a case-by-case basis based on treatment tolerability, safety, and clinical response. From principal investigator’s (PI) previous clinical experience treating patients with ketamine, dose adjustment occurs within the first 1-3 sessions, and patients continue with stable doses following sessions 2 and 3. However, dose adjustment can also occur after session 3 if the participant experiences side effects with repeated infusions. The procedure around dose adjustment is a part of this trial’s feasibility; this information will be collected by the study physician during weekly follow-ups and incorporated into the research protocol for further studies in the future.

#### Monitoring Schedule

All patients will stay on-site for the administration and monitoring period, calculated as 2 hours from the start of IV infusion per consensus guidelines in ketamine administration. Patients will stay in a separate private space and be provided with noise-cancellation headphones and an eye mask to minimize environmental disruptions. Patients will be closely monitored by available trained personnel, with a medical doctor present on-site for the entire supervision period. Specifically, IV induction will be performed under the direct supervision of an anesthesiologist or delegate and psychiatrist, who will remain present on-site for the entire duration of the 40-minute ketamine infusion. Trained personnel are available on-site to closely monitor the postinfusion period, where vital signs (ie, heart rate, blood pressure, oxygen saturation level) will be monitored every 30 minutes. Each patient will be closely monitored for the entire IV infusion duration and the postinfusion period for at least 2 hours. The overall time per treatment session is at least 2 hours starting from the time of infusion initiation. This includes the 40-minute infusion period and 80 minutes for postinfusion monitoring. Any adverse events will be managed by the medical team administering the treatment. If required, appropriate medications will be provided to manage treatment-related side effects and any adverse events as defined by clinical site policies and regulations. Clinical and neurophysiological assessments will be administered according to the trained research personnel’s schedule for study visits. There is a total of 16 study visits in this trial, which includes treatment sessions and follow-ups.

#### Potential Risks and Mitigation Strategies

Given the potential risks described below, trained medical personnel will be present during the administration and for the entire duration of the 2-hour monitoring period.

Ketamine is classified as a schedule I controlled substance due to its potential for abuse and addiction and can be abused in a number of ways, including via injection, snorting, or orally. Ketamine can produce vivid dreams and a feeling that the mind is separated from the body, referred to as “dissociation.” Regular users of ketamine can become tolerant to the dissociative effects of the drug, meaning an increasing amount is needed to achieve the same effect. Drug-related risks include (1) psychiatric symptoms such as fatigue, dizziness, anxiety, visual and auditory disturbances, panic attacks, increased irritability, and changes in mood and behavior; (2) medical symptoms such as transient increases in blood pressure and heart rate, an increase in the need to urinate, headaches, vision changes, chest pain, shortness of breath, confusion, memory impairment, anaphylaxis; and (3) a rare risk of dependency. To address these risks, in this trial, ketamine will be dispensed by the research pharmacy and administered by a trained medical professional, and the patient will receive close supervision and monitoring. Doses are individually calculated, and treatment sessions are structured to prevent tolerance building. Patients will be strongly discouraged from using ketamine outside of the context of this trial and will be informed that they can be discussed with the study physician if they have questions.

IV route–associated risks are infiltration, hematoma, air embolism, phlebitis, extravascular drug administration, and intraarterial injection. Most of these complications are transient and resolve with conservative monitoring. An intraarterial injection is rare but as threatening. An anesthesiologist is present on-site for the IV infusion and will attend if needed, per site rules and regulations.

#### Clinical Assessment Risks

Answering multiple questions at times can be distressing. These adverse reactions are mostly brief, transient, and rarely have long-term implications.

#### TMS-EMG/EEG Risks

Single-pulse TMS is now in routine clinical diagnostic use in hundreds of neurophysiological laboratories worldwide. The ability of TMS to noninvasively stimulate brain areas presents a significant advance beyond techniques that require the invasive method of direct cortical or transcranial electrical stimulation. Magnetic fields pass through the scalp and skull without the impedance encountered by direct electrical stimulation, permitting enhanced control over the site and intensity of stimulation. The induced electrical current is well below that which is expected to cause harm to nervous tissue; thus, stimulation at <1 Hz carries virtually no risk of seizure and is therefore classified as a nonsignificant risk device. In numerous studies, single-pulse TMS has been found to pose no significant health risk to properly screened healthy volunteers.

### Outcomes

The primary outcome of this pilot trial is to examine the safety and feasibility of repeated subanesthetic doses (0.5-0.8 mg/kg) of ketamine administered over 40-minute IV infusions in patients with BD to treat acute suicidality based on recruitment numbers, attrition rate, and a number of adverse events in the trial. The secondary outcome is to analyze the potential impact of ketamine on neurophysiological markers associated with cortical excitation and inhibition as a proxy of NMDA receptor activity in the cortex. The tertiary outcomes are to assess the intervention’s potential effect on clinical outcomes, such as acute suicidality, depressive symptoms, and quality of life.

### Participant Timeline

We intend to recruit 30 participants, adults 24-65 years old, diagnosed with BD and experiencing suicidal thoughts in their current episode, over the duration of 2 years from 1 site (CAMH). The trial period is shown in the CONSORT (Consolidated Standards of Reporting Trials) diagram (Figure 1).

**Figure 1 figure1:**
[figure not shown]
Flowchart of the study design.

### Sample Size

We calculated our sample size based on this study design, which is to test the safety and feasibility of ketamine infusions. We calculated that a minimum sample size of 30 participants is needed for the proposed investigation.

### Recruitment

This is a single-site open-label pilot safety and feasibility study that will be conducted at the CAMH. The CAMH is a large urban academic institution offering psychiatric care to a diverse population across the province. We intend to recruit participants through CAMH General Division Ambulatory services, which annually provides over 500 consultations for mood-related concerns. The study’s PI is a staff psychiatrist and clinician-scientist in General Division who provides outpatient services to a large population with mood disorders at local and provincial levels. PI is also an interventional psychiatrist working as a part of the Therapeutic Brain Intervention Centre, seeing many patients with treatment-resistant and severe mood disorders. She is also US certified in ketamine interventions and a member of the American Society for Ketamine Physicians (ASKP). This study group has extensive experience with recruiting patients for clinical trials as the PI of this study and coinvestigators are clinician-scientists who provide care to a large number of patients with mood disorders within the context of clinical trials. Thus, we believe recruiting 30 participants over 2 years is feasible.

In addition to group expertise, we will utilize a CAMH-wide recruitment strategy, specifically the Clinical Engagement and Research Recruitment (CLEARR) model, where all new referrals to the CAMH clinics are prescreened, and all patients are informed about clinical research at the time of their initial clinical assessment. The study site will make efforts to recruit a representative and ethnically diverse sample. CAMH services a very diverse inner-city population through numerous satellite clinics in several minority neighborhoods throughout the city. Toronto has diverse cultural representation as almost 75% of its population, aged 15 and older, have direct ties to immigration. In this study, we anticipate our recruitment will follow the ethnic distribution of White/non-Hispanic 50%, Asian 20%, Southeast Asian 15%, Black/non-Hispanic 10%, and Hispanic 5%. We also expect that 60% of our population enrolled at the CAMH site will be female based on our prior experience with clinical trials at the CAMH.

### Data Collection Methods

Data will be collected on a baseline assessment, weekly during the course of IV ketamine, within a week after the completion of the intervention, and following 4 weeks for a final follow-up. Assessments will include psychiatric assessment, physical examination, and clinical assessments through manualized validated clinical scales (Multimedia Appendices 1 and 2).

*Psychiatric assessment* will include a consultation with a study physician to confirm a diagnosis. Demographic information, medical and psychiatric history, and concomitant medications will also be included.

A *physical examination* will include a physical exam performed by a study physician or a delegate, and blood work and electrocardiography for medical clearance according to standard clinical procedures also be reviewed by the study physician. Blood tests will include complete blood count with differential tests (white blood cells, red blood cells, hemoglobin, hematocrit, mean corpuscular volume, mean corpuscular hemoglobin, mean corpuscular hemoglobin concentration, red cell distribution width, mean platelet volume, platelet, nucleated red blood cell count, neutrophil count, lymphocyte count, monocyte count, eosinophil count, basophil count); blood chemistry test, including liver function (alanine transaminase and aspartate transaminase), kidney function (blood urea nitrogen and creatinine), and electrolytes (sodium, potassium, chloride, and phosphate); and thyroid function (thyroid-stimulating hormone). Study participants’ blood pressure will also be monitored before, during, and after treatment.

*Clinical assessments* will include (1) the MINI to clarify psychiatric inclusion and exclusion criteria; (2) the Antidepressant Treatment History Form (ATHF) to clarify on inclusion and exclusion criteria [26]; (3) the SSI will be administered at screening, baseline, weekly, and after treatment to confirm eligibility and to assess changes as a secondary outcome measure; (4) the HRSD-24, which will assess changes in depressive symptoms and will be administered at the baseline and after treatment; (5) the Young Mania Rating Scale (YMRS), which will be used to evaluate mania/hypomania symptoms at screening and throughout the study for eligibility and safety monitoring purposes [27]; and (6) World Health Organization Disability Assessment Schedule (WHODAS 2.0), which will be used as a standard measure of disability promoted and used at baseline and after treatment to assess changes in individual level of functioning [28].

*Neurophysiological assessments* will include (1) the Transcranial Magnetic Stimulation Adult Safety Screen to assess potential TMS risk factors; and (2) TMS-EMG/EEG. Our neurophysiological measures have been established and have a high test-retest reliability (ie, intraclass correlation >0.9) [18,19]. Data analysis will be performed using semiautomated methods developed and validated by our group [29]. TMS pulses will be administered to the left dorsolateral prefrontal cortex using a 7-cm figure-of-eight coil and 2 Magstim 200 stimulators (Magstim Company Ltd) connected via a BiStim module, and motor-evoked potential data will be collected using commercially available software (Signal; Cambridge Electronics). Each TMS session will include the establishment of the individual threshold for stimulation of motor cortex, and dorsolateral prefrontal cortex localization will be performed according to previously published methods [29,30]. The resting motor threshold will be determined by applying single pulses of TMS to the motor cortex while the coil is placed at the optimal position to elicit motor-evoked potentials from the right abductor pollicis brevis muscle. The resting motor threshold is defined as the minimum stimulus intensity that elicited a motor-evoked potential of >50 μV in more than 5 of the 10 trials [30].

TMS-EMG will be recorded from the abductor pollicis brevis with Ag-AgCl electrodes placed over the belly of the muscle. The signal will be amplified (Model 2024F; Intronix Technologies Corporation), filtered (band-pass 2 Hz-5 kHz), digitized at 5 kHz (Micro 1401; Cambridge Electronics Design), and stored in a laboratory computer for offline analysis. The participants will be instructed to relax throughout the study. Trials contaminated with voluntary muscle activity will be discarded.

### TMS-EEG

EEG will be used to evaluate TMS-induced cortical evoked activity. EEG recordings will be acquired through a 64-channel EEG system [30]. A 64-channel EEG cap will be used to record the cortical signal, and 4 electrodes will be placed on the outer side of each eye and above and below the left eye to closely monitor the eye movement artifact. All electrodes will be referenced to an electrode placed on the vertex positioned posterior to the Cz (midline central) electrode. Direct current EEG signals will be recorded with a 20-kHz sampling rate and with a low-pass filter of 300 Hz, which in pilot experiments was shown to avoid saturation of amplifiers and minimize the TMS-related artifact. The EEG data will be downsampled to a 1-kHz sampling frequency and segmented concerning the TMS stimulus such that each epoch includes a 1000-ms prestimulus baseline and a 1000-ms poststimulus activity. Epochs will be baseline corrected concerning the TMS-free prestimulus interval. The baseline-corrected poststimulus intervals (approximately 25-1000 ms) that are not contaminated by TMS artifact will be extracted and digitally filtered using a zero-phase shift 1-100-Hz band-pass filter (48 dB per octave). Records will be manually reviewed at this stage, and trials contaminated with muscle activity, movement, and TMS artifacts will be excluded from further analysis. Finally, the average signals at each recording site will be computed from the movement-free epochs (approximately 80 trials per participant) and fed into an automated eye-blink correction algorithm [30]. The eye-blink–corrected average EEG waveforms will be imported into MATLAB (The MathWorks Inc), and further analyses will be carried out using the EEGLAB toolbox [31]. Furthermore, methods in this approach will be conducted according to previously published combined TMS-EEG studies [29-31].

### Data Management

The REDCap (Research Electronic Data Capture) software will be used for data collection and overall study data management throughout this project. REDCap is a secure, web-based clinical data management and electronic data capture system and database. It is built and distributed by Vanderbilt University, with a local instance installed on a central CAMH server overseen by the CAMH REDCap Operations Committee. All data are stored on-site and backed up daily. The system is developed and managed in compliance with HIPAA (Health Insurance Portability and Accountability Act), PIPEDA (Personal Information Protection and Electronic Documents Act), and FDA21 CFR (US Food and Drug Administration Code of Federal Regulations Title 21) Part 11 regulations, providing functions such as defined user roles and privileges, user authentication and encryption, electronic signatures, deidentification of protected health information, comprehensive auditing features to record and monitor access and data changes, and a validated software development life cycle. This system will collect data, design electronic case report forms, data entry, monitor and clean, and query and export data sets for statistical analysis.

### Statistical Methods

Baseline participant characteristics will be reported and described using summary statistics—mean and SD for continuous data and number and proportion for categorical data. As the primary outcome is to assess feasibility, we will report on (1) recruitment numbers and attrition rates; (2) the number of individuals who experience side effects, and (3) the overall number and type of side effects. For neurophysiology, we will use an independent *t* test (paired 1-tailed) to compare components of TMS-evoked responses in the left dorsolateral prefrontal cortex in TMS-EEG data. In addition, we will apply a nonparametric cluster-based permutation test to investigate any significant changes in overall EEG channels. We will conduct a paired 1-tailed *t* test of the SSI and HRSD-24 scores from baseline to week 4 and monthly follow-up to assess preliminary clinical outcomes. We will also report the standardized mean difference as a measure of effect size (small: 0.2; medium: 0.5; large: 0.8).

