### Limitations

In general, a lack of a control group and a small sample size are limitations in ketamine clinical trials. However, given that this is a pilot open-label clinical trial, the sample size is sufficient (ie, the goal is not to assess generalizability or statistical significance). The lack of blinding in the control group is a common concern in ketamine trials because a placebo with comparable effects does not exist, and it is impossible to ensure blinding to the full extent. Because the study is conducted at a single site of a large psychiatric academic facility, the results may not be fully transferable to a broader population; however, the study will provide preliminary data on feasibility and safety to be used in a larger, adequately powered and controlled trial. Moreover, a small sample size may not allow drawing any meaningful conclusions around neurophysiological markers of response; however, results will inform a further larger clinical trial where we can test neurophysiological markers more accurately.

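### SSI and HRSD-24 change are tested one-tailed with no stated alpha, direction or reason; if the tail points to improvement, these tests cannot find significant worsening

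*Protocol article*

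**What the plan says.** The Statistical Methods section of the protocol article states: "We will conduct a paired 1-tailed *t* test of the SSI and HRSD-24 scores from baseline to week 4 and monthly follow-up". The purpose given is "to assess preliminary clinical outcomes". No significance level, tail direction or reason for one-tailed testing follows. The same paragraph adds an effect size: "We will also report the standardized mean difference as a measure of effect size (small: 0.2; medium: 0.5; large: 0.8".

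The Outcomes section makes safety and feasibility primary, judged on recruitment, attrition and adverse events. It ranks the clinical scales lower: "The tertiary outcomes are to assess the intervention’s potential effect on clinical outcomes, such as acute suicidality, depressive symptoms, and quality of life". The Limitations section acknowledges the missing control group and, in explaining why the sample size suffices, says that "the goal is not to assess generalizability or statistical significance". The Sample Size section gives 30 participants. Entry requires an SSI of at least 9 and an HRSD-24 of at least 14 (Eligibility Criteria).

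**The concern.** A one-tailed test is defensible when a result in the other direction would be of no interest. That is hard to argue here. Participants enter with suicidal ideation, safety is a primary objective, and a rise in SSI or HRSD-24 is something the investigators would want to know about. A test that looks only for improvement returns a p-value near 1 for clear average worsening, and a reader of the results table would see only a non-significant result.

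Depending on the alpha used, one tail also lowers the bar for declaring benefit. The pre-post result is meant to inform a larger trial, so a lenient threshold could carry a weak signal forward.

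Sidedness is something the article states, so this is not detail left to an analysis plan that is not shown.

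**Working it through.** **Inputs.** From the article: paired one-tailed t tests, two scales (SSI, HRSD-24), two comparisons (baseline to week 4, baseline to the monthly follow-up), n = 30, no control group. Assumed because not stated: the tail points to improvement; one-sided alpha is 5%, with 2.5% and 1% shown as a range; all 30 participants give paired data. The article gives no operating figure for these tests. Its 30 comes without alpha, power or effect size, so there is nothing to reproduce.

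**Step 1: what the test does with worsening.** Write dz for mean change divided by the SD of change, so that t = dz × √n on n − 1 = 29 df. For an observed worsening of dz = 0.5, |t| = 0.5 × √30 = 2.74.
- One-tailed toward improvement: p = P(T29 > −2.74) = 0.995.
- Two-sided: p = 2 × P(T29 > 2.74) = 0.010.

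If the true worsening is dz = 0.5 (noncentral t, noncentrality 2.74 in the wrong direction), the two-sided 5% test declares worsening with probability 75.4%. The one-tailed test rejects with probability below 0.00001, and any such rejection would be a claim of benefit. With fewer completers (assumed), the two-sided figure is 65.0% at n = 24 and 56.4% at n = 20.

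**Step 2: false benefit per test.** Under no change, the chance of declaring benefit equals the area in the benefit tail. A two-sided 5% test has 2.5% there.

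| One-sided alpha (assumed) | False-benefit rate | Ratio to two-sided 5% |
|---|---|---|
| 5% | 5% | 2.0 |
| 2.5% | 2.5% | 1.0 |
| 1% | 1% | 0.4 |

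A simulation of 400,000 null trials with n = 30 gave 4.98% for the one-sided 5% test and 2.45% for the benefit tail of the two-sided 5% test.

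**Step 3: false benefit over the four tests.** If independent:
- one-sided 5%: 1 − 0.95⁴ = 18.5%
- two-sided 5%, benefit direction only: 1 − 0.975⁴ = 9.6%

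The tests share patients and a common baseline, so positive correlation is likely and both figures would then be lower.

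**Step 4: cost of two sides.** At n = 30 the critical t rises from 1.699 to 2.045, and the smallest significant observed dz from 1.699/√30 = 0.310 to 2.045/√30 = 0.373. Power at dz = 0.5 falls from 84.8% to 75.4%. The effect detectable with 80% power (noncentral t) rises from 0.465 to 0.529.

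**Step 5: what an interval would show.** The half-width of a two-sided 95% interval is 2.045/√30 = 0.373 SD of change. For the worsening in Step 1 the interval runs from 0.5 − 0.373 = 0.127 to 0.5 + 0.373 = 0.873 SD of change in the wrong direction, which displays the harm plainly.

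**The case against.** The best defence is that these tests are not the safety analysis. Safety is judged on adverse events and attrition, reported descriptively. Average worsening would appear in the sign of the standardized mean difference. The Discontinuation Criteria cover a 50% rise in HRSD-24, hospitalization for suicidality and physician-judged worsening. Adverse events are collected until 30 days after the last dose. A reader might infer that worsening cannot register anywhere in the trial; the article does not support that. This part of the defence stands, with two limits. No discontinuation criterion uses the SSI score. The HRSD-24 criterion needs two consecutive ratings, while Data Collection Methods lists that scale only at baseline and after treatment, and these passages should be reconciled.

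Second, a reader might infer that false claims of benefit are twice as likely. That holds only at one-sided 5%, and the article states no alpha. Nor does 18.5% by itself measure the harm of one tail: four independent two-sided 5% tests have the same chance of an error in either direction. The fair comparison is 18.5% with 9.6%.

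Third, the remark in Limitations about statistical significance might be read as contradicting the tests. It explains why the sample suffices for a pilot, and tests labelled preliminary are compatible with it. The SSI is called a secondary measure in Data Collection Methods ("to assess changes as a secondary outcome measure") but acute suicidality is tertiary in Outcomes. That is a labelling slip that changes no analysis. The denominator of the effect size is ordinary analysis-plan detail.

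Finally, regression to the mean after entry on raised scores affects a two-sided test just as much. True, so sidedness alone cannot make the result interpretable as efficacy.

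**Conclusion.** The point holds as a poor stated choice on preliminary, lower-tier outcomes. It does not threaten the primary objective. If the tail points to improvement, the planned tests cannot declare worsening of SSI or HRSD-24 significant, however large it is. If the tail pointed the other way, they could not declare benefit, and either way the article should say. Inflation of false benefit is conditional: 5% against 2.5% per test at an assumed one-sided 5%, none at one-sided 2.5%. The four-test figures also assume independence. Nothing here shows that harm would go unseen in the trial as a whole, and two-sided testing would not turn an uncontrolled pre-post change into evidence of efficacy.

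**What to change.** In Statistical Methods, replace the one-tailed tests of SSI and HRSD-24 with two-sided ones and state the alpha. Report mean change in scale points with two-sided 95% confidence intervals at week 4 and at the monthly follow-up as the main preliminary clinical result. Add the number of participants whose scores worsened on each scale. State that, without a control group, no pre-post change will be read as evidence of efficacy.

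The cost is a change of wording and a small loss of sensitivity (Step 4 of the working). That matters little in a pilot that does not aim at significance. No extra participants or assessments are needed.
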